**Fig. 2 Fig2:**
[figure not shown]
The procedures that participants will undergo at T0, T1, and T2

### Participants

In total, 24 individuals with MS will be recruited from the two participating MS centers (12 from each center). Recruitment of participants will be handled by advertisement and awareness of the trial through the medical staff of each participating center.

#### Inclusion criteria

Diagnosis of MS according to the revised McDonald Criteria 2017 [28]Aged 25–60 years oldAn Expanded Disability Status Scale score ≥ 6 [29]An ability to understand and execute simple instructionsA cut-off score of > 0.5 pegs/s (=18 s) on the nine-hole peg test (NHPT) (selected due to its high discriminative and predictive ability in distinguishing ADL independence in PwMS) [7]

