Therefore, the primary goal of the TEAMS (TElerehabilitation And Multiple Sclerosis) is to implement a single-blind, RCT designed to compare the effectiveness of an 8-week home-based telerehab VR program with conventional therapy in PwMS with manual dexterity difficulties. Secondary aims include (a) evaluating the impact of the programs on quality of life after the intervention and follow-up 1 month later and (b) evaluating the impact of the programs on adherence and satisfaction. A tertiary aim will be to generate effect sizes which can be used to power a larger clinical trial aimed at improving upper limb functional activities via telerehab in PwMS in Italy and Israel. We hypothesize that there will be no difference in outcomes between a home-based telerehab VR training program aimed at improving functional activities of the upper limbs compared with a conventional clinic-based program after the intervention and follow-up 1 month later. We also intend to corroborate a secondary hypothesis that performing the telerehab VR training will lead to better outcomes in quality of life and adherence to upper limb exercise.

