#### Sample size

The sample size is based on Julious’s [31] recommendation that the rule of thumb for a pilot study is a sample size of 12 subjects per group. The justifications for this sample size are based on rationale relating to feasibility, mean and variance precision, regulatory considerations, and the expected change in the study’s primary outcome measure (NHPT). According to the literature, a 20% change in the NHPT demonstrates a clinically meaningful worsening in PwMS [32]. In our study, power will be set at 80% and alpha at 5%. Therefore, 24 subjects (12 in each group) will be required in order to detect differences between the two treatment groups (assuming non-inferiority with moderate correlations among covariates, *r*-squared = 0.50).

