### Outcomes

#### Primary outcomes (collected at T0, T1, T2)

##### NHPT

The NHPT was selected based on the widespread adoption and extensive data available. Furthermore, the NHPT is recommended as a gold standard for measuring manual dexterity in PwMS [32]. The NHPT has excellent psychometric properties as to reliability, discriminant, concurrent, and ecological validity; can detect progression over time; is sensitive to treatment; and, as such, is recommended for inclusion in clinical trials. Briefly explained, the NHPT requires participants to repeatedly place nine pegs into nine holes, one at a time, as quickly as possible and then remove them from the holes. The total time needed to complete the task is then recorded. Two consecutive trials with the dominant hand are immediately followed by two consecutive trials with the non-dominant hand [4, 8].

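### The NHPT inclusion criterion puts its inequality on the speed scale, so as written it admits people faster than 18 s and contradicts the stated population with manual dexterity difficulties

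*Protocol article*

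**What the plan says.** The Inclusion criteria section of the protocol article lists, among the conditions for entry, a "cut-off score of > 0.5 pegs/s (=18 s) on the nine-hole peg test (NHPT"). The reason given is that the cut-off was "selected due to its high discriminative and predictive ability in distinguishing ADL independence in PwMS".

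The Background section gives the trial's primary goal as comparing a "home-based telerehab VR program with conventional therapy in PwMS with manual dexterity difficulties". The Abstract describes the population in the same way.

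The NHPT entry under Primary outcomes says that "the NHPT requires participants to repeatedly place nine pegs into nine holes, one at a time, as quickly as possible", and then remove them. It adds: "The total time needed to complete the task is then recorded". The NHPT is therefore both an entry condition and the primary outcome.

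**The concern.** The criterion expresses the threshold as a rate and gives a time as its equivalent. The two scales run in opposite directions: better performance is a higher rate and a shorter time. The only inequality in the criterion is a greater-than sign, and it is attached to the rate. The time carries an equals sign, so it does not set a direction of its own. As a condition for entry, the sentence asks for people on the fast side of the cut-off, while the aims describe people with impaired dexterity.

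This line is the only listed criterion that refers to hand function as something a participant must show. The others cover diagnosis, age, the Expanded Disability Status Scale (an overall disability score), ability to follow instructions, comorbidity, cognition, pregnancy, vision, and recent relapse or treatment. If its direction is wrong, no other criterion selects the intended population.

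The direction also bears on interpretation. The Background hypothesises no difference between programs, the Sample size section assumes non-inferiority, and the Discussion would read comparable results as support for letting patients choose either program. A sample with less scope to change on the NHPT could push the two arms towards similar results for reasons unrelated to the programs. It could also affect the effect sizes that the tertiary aim wants for planning a larger trial.

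**Working it through.** **Inputs**

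- Cut-off: a rate above 0.5 pegs/s, stated as equal to 18 s (Inclusion criteria).
- Number of pegs: nine (NHPT under Primary outcomes).
- Scoring: total completion time, performed as fast as possible, so a shorter time is better (same place).
- Population: people with MS with manual dexterity difficulties (Abstract and Background).

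**Step 1: reproduce the plan's own figure.** Time = pegs / rate = 9 / 0.5 = 18.0 s. In the other direction, 9 / 18 = 0.5 pegs/s. The conversion is exact, and it shows that the article counts nine pegs per test.

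**Step 2: direction.** Rate = 9 / time falls as time rises. A rate above 0.5 pegs/s is therefore the same as a time below 9 / 0.5 = 18 s.

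**Step 3: who enters.** The last two columns compare the criterion as written with the reversed inequality.

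| Time (s) | Rate = 9 / time (pegs/s) | As written (> 0.5) | Reversed (< 0.5) |
|---|---|---|---|
| 12 | 0.750 | admitted | not admitted |
| 15 | 0.600 | admitted | not admitted |
| 17.9 | 0.503 | admitted | not admitted |
| 18 | 0.500 | not admitted | not admitted |
| 18.1 | 0.497 | not admitted | admitted |
| 22.5 | 0.400 | not admitted | admitted |
| 30 | 0.300 | not admitted | admitted |
| 60 | 0.150 | not admitted | admitted |

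The decision reverses at every time except exactly 18 s, which satisfies neither strict inequality.

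**Step 4: set against the population.** As written, every admitted person is faster than every person excluded for being slower than 18 s. A trial in people with dexterity difficulties needs the slower side. The threshold is not restated anywhere else in the article, so no other text corrects the direction.

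The calculation uses no power, alpha, margin or standard deviation, and it leaves the sample size of 24 as it stands.

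**The case against.** The strongest reply is that this is a slip of notation and nobody chose to enrol fast performers. The Abstract and Background state the population plainly, the numerical threshold is right, and the NHPT is recorded as a time. Experienced staff at two established MS centers might well read the line as longer than 18 s. The phrase cut-off score is itself a little loose. Much of this stands: the intended direction can be inferred, and the defect is best described as an internal inconsistency. It does not rescue the criterion, because an entry rule that works only when read against its own symbol is wrong as written.

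Three stronger readings are tempting, and the document does not support them.

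- A reader might infer that all 24 participants will come from the wrong side, or that the two centers will recruit opposite populations. The first requires both sites to apply the sign literally. The second requires them to apply it differently. Nothing in the article shows that either will happen.
- A reader might infer that people under 18 s have preserved dexterity and almost no room to improve, so that a finding of no difference would be false. The article gives no NHPT distribution, norm or standard deviation, and the source cited for the cut-off was not available. Reduced scope for change is plausible but cannot be sized.
- A reader might add that the criterion does not name the hand. That is a separate detail which a condensed article may leave to the full protocol, and it is not part of this point.

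**Conclusion.** Wrong as written (internal inconsistency). The criterion's inequality contradicts the stated population, and following it literally selects the opposite side of the 18 s cut-off: 15.0 s (0.6 pegs/s) qualifies and 22.5 s (0.4 pegs/s) does not. This rests only on the article's own conversion, its description of the test and its statement of the population.

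The consequence is conditional. If a site applied the criterion literally, it would enrol people outside the intended group. That could reduce scope for change on the primary outcome and could favour apparent similarity between the arms. Neither effect can be quantified from the document. The point still needs correcting, because the error lies in a decision threshold and no other criterion compensates for it.

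**What to change.** Reconcile the inclusion criterion with the stated population by giving both scales with matching inequalities: NHPT speed below 0.5 pegs/s, i.e. completion time longer than 18 s. Before first enrolment, confirm that the eligibility form at both centers uses the same direction.

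The cost is a one-line text correction and a check of the form. The Trial status section says that the trial has not begun, so on the article's account nobody has been enrolled under this wording. The correction changes neither the sample size nor the analysis.

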#### Exclusion criteria

Orthopedic and other neurological disorders affecting upper limb movements (e.g., epileptic seizures)Contra-indication to physical activity (e.g., heart failure, severe osteoporosisModerate or severe cognitive impairments as indicated by the Mini-Mental State Examination [30] score < 21Pregnancy (self-reported)Severe uncorrected visual deficitsMS clinical relapse or treatment with corticosteroid therapy within 90 days prior to enrollmentStarted or stopped a disease-modifying therapy for MS within 90 days prior to enrollmentPatients who received a course of physical or occupational therapy (home, outpatient, or inpatient) within the past 30 daysOther treatments that could influence the effects of the interventions. PwMS eligible for participation will be informed of the study by their rehabilitation specialist, both orally and in writing. All participants will provide written informed consent.

#### Sample size

The sample size is based on Julious’s [31] recommendation that the rule of thumb for a pilot study is a sample size of 12 subjects per group. The justifications for this sample size are based on rationale relating to feasibility, mean and variance precision, regulatory considerations, and the expected change in the study’s primary outcome measure (NHPT). According to the literature, a 20% change in the NHPT demonstrates a clinically meaningful worsening in PwMS [32]. In our study, power will be set at 80% and alpha at 5%. Therefore, 24 subjects (12 in each group) will be required in order to detect differences between the two treatment groups (assuming non-inferiority with moderate correlations among covariates, *r*-squared = 0.50).

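### The sample-size paragraph presents a rule-of-thumb pilot size as the requirement for 80% power, but that power does not follow from the inputs it states

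*Protocol article*

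**What the plan says.** The Sample size section of the protocol article starts from a published recommendation that "the rule of thumb for a pilot study is a sample size of 12 subjects per group". It supports this with feasibility, precision of the mean and variance, regulatory considerations and the expected NHPT change. It then reports from the literature that "a 20% change in the NHPT demonstrates a clinically meaningful worsening in PwMS" and states that "power will be set at 80% and alpha at 5" per cent. The last sentence opens with *Therefore* and concludes that "24 subjects (12 in each group) will be required in order to detect differences between the two treatment groups", with the qualification "assuming non-inferiority with moderate correlations among covariates" and an r-squared of 0.50.

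Three other places bear on this:
- The Background section hypothesises no difference in outcomes between the two programmes. It also says: "A tertiary aim will be to generate effect sizes which can be used to power a larger clinical trial".
- The Statistical analysis section plans a Condition × Time MANOVA followed by univariate F-ratios, with effect sizes as eta-squared and Cohen's d and the cognitive battery scores as covariates.
- The Discussion would read comparable results as letting patients choose either programme.

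**The concern.** A calculated sample size needs a difference or margin, a standard deviation and a sidedness. The paragraph supplies none of these as such, yet presents 24 as the consequence of 80% power and 5% alpha. The 20% is described as a threshold for meaningful worsening, and nowhere is it declared as an acceptable difference between arms. Detecting a difference and showing non-inferiority are separate objectives with separate calculations, and the sentence names both. The analysis section then describes only tests of difference, so the power statement attaches to a comparison that the described analysis does not make.

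What is at stake is how the result is read. The hypothesis is no difference, and the Discussion would act on comparability. A reader who trusts the 80% could take a non-significant F-test in 24 patients as adequately powered evidence that the programmes are equivalent. The tertiary aim adds to this by carrying a very imprecise effect size into the next trial.

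**Working it through.** **Can 24 be reproduced?** Not from the stated inputs: without an SD and a margin no forward calculation can be run. The only source on the page that yields 12 per group is the rule of thumb. The check therefore runs backwards: what would have to be true for 12 per arm to give 80% power?

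**Inputs**
- From the Sample size section: n = 12 per arm, power 80%, alpha 5%, r-squared 0.50.
- Assumed: alpha is one-sided 5% or one-sided 2.5%, since sidedness is not stated.
- Assumed: the margin is 20% of the NHPT mean, since the 20% is not declared as a margin.
- Assumed: the true difference is 0, in line with the stated hypothesis.
- Assumed: r-squared 0.50 is the share of outcome variance that the covariates explain. The text says "moderate correlations among covariates, *r*-squared = 0.50", but correlation among covariates does not itself reduce residual variance; only covariate-outcome correlation does.

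**Formula.** Residual SD = SD × √(1 − 0.50) = 0.707 SD. With d = margin / residual SD, the noncentrality is d × √(12/2) = 2.449 d. Power is the probability that a noncentral t with 21 df exceeds the critical value, which is 1.721 (one-sided 5%) or 2.080 (one-sided 2.5%).

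**Margin needed for 80% power**
- One-sided 5%: d = 1.049, so the margin is 1.049 × 0.707 = 0.742 SD. A margin of 20% of the mean then requires SD ≤ 0.20 / 0.742 = 27% of the mean.
- One-sided 2.5%: d = 1.200, so the margin is 1.200 × 0.707 = 0.848 SD, and SD ≤ 0.20 / 0.848 = 24% of the mean.
- The normal approximation gives nearly the same limits, 28% and 25%.

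**Power at 12 per arm over an assumed range of SDs** (margin 20% of the mean, R-squared 0.50)

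| SD as % of mean | One-sided 5% | One-sided 2.5% |
|---|---|---|
| 20 | 96% | 91% |
| 25 | 85% | 75% |
| 30 | 72% | 60% |
| 40 | 51% | 38% |
| 50 | 38% | 26% |

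Example row: at SD 40%, d = 0.20 / (0.40 × 0.707) = 0.707 and the noncentrality is 1.732, which gives 51% and 38%.

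**If the covariates explain nothing** (R-squared 0, 22 df), the SD limit falls to 19% of the mean (one-sided 5%) or 17% (one-sided 2.5%). At SD 30%, power is 48% or 35%.

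**What 24 patients do provide**
- 95% CI half-width for the difference between arms: 2.080 × √(2/12) × 0.707 SD = 0.60 SD with R-squared 0.50, and 2.074 × √(2/12) SD = 0.85 SD with R-squared 0.
- 95% CI for Cohen's d at an observed d of 0: about ±1.96 × √(2/12) = ±0.80.
- 95% limits for the SD on 22 df: √(22/36.78) = 0.77 to √(22/10.98) = 1.42 times the estimate.

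**The case against.** The strongest reply is that this is a labelled pilot whose first justification is the rule of thumb, together with feasibility and precision. On that basis 24 stands without any power statement. This is right, and it is why the sample size itself is not challenged. It does not rescue the sentence that derives 24 from 80% power.

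A second reply is that a journal article condenses a fuller protocol, which may hold the SD, its source and an attrition allowance. That is accepted for attrition and for the source of the SD, and neither is counted here. The difficulty is different: the article itself states a power, a required number and an inference from one to the other, and it mixes two objectives in one sentence.

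A third reply is that the reference to covariates is loose phrasing. Probably so, and the calculation above takes the favourable reading.

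Two stronger readings are tempting and should be resisted:
- A reader might infer that NHPT times vary too much between patients for 80% power to be realistic. The documents give no SD, mean or coefficient of variation for the NHPT. The entry criteria (a single NHPT cut-off and an EDSS threshold) do not yield one. At an SD of 20% of the mean the stated power is exceeded; at 25% it is met at one-sided 5% and just missed at one-sided 2.5%.
- A reader might infer that the tertiary aim must fail because every expected effect is zero and the next trial is a non-inferiority trial. The article does not state the design of that trial, and it hypothesises better quality of life and adherence with the telerehabilitation programme. What remains is the imprecision of the observed effect size.

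**Conclusion.** The point holds as an inconsistency in the justification, not as a demonstrated shortage of power. The 80% does not follow from what the paragraph states, and the non-inferiority comparison it refers to is not among the analyses described. Whether the trial has 80% power depends on four things the paragraph does not settle: the margin, the sidedness, the NHPT SD, and whether the covariates really explain half the outcome variance. With a 20% margin, a true difference of zero and R-squared 0.50, the claim needs an SD no larger than about 27% or 24% of the mean. Across assumed SDs of 20% to 50%, power runs from 96% down to 38% at one-sided 5%, and from 91% down to 26% at one-sided 2.5%. The practical consequence is that a non-significant result should not be presented as adequately powered evidence of comparability.

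**What to change.** Keep 24 patients. Delete the 80% power statement and the *Therefore*, and rest the size on the pilot rationale already given, expressed as precision: a 95% CI half-width for the NHPT difference of about 0.60 SD if covariates explain half the variance, and 0.85 SD if they explain none. State that a non-significant difference will not be read as showing comparability.

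If a power figure is kept, choose one objective and give the margin, its scale, the SD, the sidedness and the covariate-outcome R-squared, with the power those values produce. If that objective is non-inferiority, the Statistical analysis section should include the matching comparison of a confidence limit with the margin.

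Reword the tertiary aim so that the pilot supplies the NHPT SD with its confidence limits (0.77 to 1.42 times the estimate) and the baseline correlation. Size the larger trial on a prespecified margin or difference, not on the observed Cohen's d.

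The cost is text only, with no extra patients or procedures. The article reports that the trial had not begun, so the change could be made before enrolment. The downside is a less favourable stated figure.

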#### Interventions

Both interventions will focus specifically on functional upper limb exercise training and be administered by experienced physiotherapists or occupational therapists with at least 2 years of professional experience in the field of neurorehabilitation. Therapists at each site will receive training protocols to ensure homogeneity of treatment between sites.

#### Telerehab VR intervention

The telerehab VR intervention consists of a custom-made software program, that will run on a personal computer (or tablet), developed under Unity (Unity Technologies Inc., San Francisco, USA). Unity is a cross-platform game engine worldwide adopted to create three-dimensional, two-dimensional, virtual reality, and augmented reality games, as well as simulations and other experiences. PwMS will be requested to perform several ADLs from the three main areas of self-care, dressing, and meal preparation. Taking place in a realistic home scenario, the PwMS will pick up objects and move them to a predefined target clearly indicated on the screen. Hand and object trajectory are controlled by a low-cost non-contact infrared controller (Leap Motion). This instrument was proven successful in upper limb rehabilitation of individuals with neurologic and orthopedic conditions [33–35].

During the exercise, the hand coordinates will be continuously recorded; thus, data kinematic data calculated on the basis of the 3D trajectory like speed, accuracy on target placement, and movement smoothness will be accessible. This data will be stored in the PC/tablet and will also be sent remotely to the clinical center for further analysis/processing. Both target position and task complexity will define the exercise difficulty, which can be modified (i.e., increased or decreased) automatically on the basis of the previous performance or manually modified by the user. A suitable period of familiarization with the installation/management of the hardware and software will be carried out under the supervision of engineers and therapists to ensure that the exercises are being correctly performed. A schematic representation of the system is shown in Fig. 3.

**Fig. 3 Fig3:**
[figure not shown]
Schematic representation of the system

#### Conventional therapy

Conventional therapy will focus on task-related upper-limb treatments while in sitting denoting the standard care for PwMS [2]. Several manual techniques, therapy tools and objects of ADL will be allowed during treatment. Use of additional electrical or mechanical therapy devices (i.e., support arm systems, splints) will be avoided. The interventions will be conducted on a one-on-one basis in the physiotherapy or occupational therapy department of each participating center. Training and therapy content will be tailored to each participant’s preferences, the agreed movement aims and their motor function level.

